### 3. Outcome:

**1)** antibody response as a result of natural malaria infections; **2)** malaria incidence; **3)** treatment incidence density (treatments per time at risk); **4)** prevalence of malaria parasitemia and parasite density for each group that received BK-SE36 vaccine (at half or full dose) and those who received placebo or no administration (control group); **5)** change in antibody titres/epitope recognition against synthetic short peptides *spanning the whole length of SE36*.

**4. Study site:** Lira Medical Centre (LMC), Lira, Uganda

**5. Study design:** Longitudinal observational study in children who participated in the BK-SE36 malaria vaccine trial in Uganda.

**6. Participants:** BK-SE36 Phase1b Stage2 study subjects (6-20 y old) who give consent for additional 11 months follow-up period, AND additional volunteers for recruitment to achieve an equal number of subjects in the control group (*i.e.* BK-SE36 cohort ( $n=66$ ) = placebo cohort + *additional volunteers* ( $n=66$ )). These additional volunteers that did not participate in Phase 1b Stage2 trial will not be receiving any intervention/administration.

**7. Number of participants:** A total of 132 participants.

(33) subjects = administered with half dose SE36 (50 µg)

(33) subjects= administered with full dose SE36 (100µg)

(9) subjects = administered with half dose of placebo (0.5mL physiological saline)

(9) subjects = administered with full dose of placebo (1.0mL physiological saline)

(48) additional volunteers to be recruited into the control group (no administration)

**8. Expected start date:** End of 40 days surveillance period of Phase 1b, Stage2

**9. Primary completion date:** 11-months after study start

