### **A4. Endpoints: Primary**

A4.1. Change in titers of anti-SE36 antibody, parasitemia rates, malaria incidence, malaria treatment incidence density

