### D. Detailed description of study visits:

**Study practice:** Medical interview, consultation and serum sampling once every four weeks for 11 months

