#### At each monthly visit:

- 1 Consultation/examination of injection site (for administered subjects) if there are unresolved AEs
- 2 Consultation interview for recent illness, malaria symptoms; includes capturing malaria incidences between visits
- 3 Vital signs (temperature, blood pressure, pulse rate)
- 4 A few drops of blood sampling (by finger prick) for malaria smear, filter paper blots, and ELISA assay.
5. Blood draw (4 mls) of venous blood for serum sampling

Subjects will be assigned to fall into different consultation days. Clinic visits will be in groups. Care should be exercised whenever possible that the BK-SE36 administered cohort group can be matched to a control cohort group in the same locality for equal "bias" in malaria incidence rates.

During this follow-up period, adverse events will not be reported but malaria episodes will be documented and blood samples collected for immunological testing. Daily body temperature monitoring and recording by participants or parents /guardians will be carried out by the participants themselves at home throughout the study period. Training of participants and /or parents/guardians in the use of thermometers, reading and recording of body temperatures will be conducted during the start of the study

At the final visit:

Blood sampling (20-ml venous blood) for ADCl and ELISA assays

Passive follow-up for malaria will consist of visits to LMC trial site whenever the subject is sick. During each visit, the subject will be evaluated and a malaria smear will be done whenever malaria is suspected. During the course of evaluation for malaria, other illnesses maybe uncovered in the study subjects, such as upper respiratory infections, and other bacterial or viral infections. The pharmacy can provide subjects with common over-the-counter analgesics such as paracetamol as well as antibiotics for the treatment of minor ailments and infections. If further evaluation or treatment is necessary, the subject will be referred to the hospital arm in LMC.

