**E. Statistical considerations**

The purpose of this study is to estimate malaria episodes, patterns of immune responses as well as compare these rates and patterns in different doses/interventions of the study based on the Phase 1b, stage2 protocol. Listings will show all observed data. Should there be a need for early termination of the study, available data will be analyzed and interpreted in light of early termination.

To assess and compare the duration of specific antibody response to SE-36 over a 11 month period:

1. A test will be performed to check for any significant differences in the antibody concentrations of the two dose groups.

2. Immunogenicity responses by vaccine and dose group will be described over time. Individual responses can also be described over time and stratified by dose cohort.
3. For antibody concentrations measured, a longitudinal model will be built to describe the antibody response over time. The model will also explore if there are any differences between the two doses used for Stage2.
4. Waning will be assessed by comparing levels of antibody with time, as well as malaria infection.
5. Average parasitemia in all samples collected during the whole period will be compared between the vaccine and placebo group (including number of incidences of mild and severe malaria in BK-SE36 vs. control groups). Kaplan-Myer plots will be used to compare the immunological protection between blood parasitemia levels and administration of BK-SE36

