| 3. Treatment obtained:  In another hospital  In the trial site previous visit
Details (include self medications)                                                                                                                                                                                                                                                                                                                                                                                                                                                                                                                                             |
| Presenting features:
 Fever  Malaise  Headache  Joint pains
 Vomiting  Cough  Diarrhoea  Respiratory Distress
 Pallor  Jaundice  Bleeding  Abdominal Pain
 Sweating  Bleeding  Convulsions  Drowsy/Lethargy
 Rigor  Other (please specify) _____ |
| Blood smear:  Negative  Positive _____                                                                                                                                                                                                                                                                                                                                                                                                                                                                                                                                                                                                                          |

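### The parasitaemia comparison in Section E pools scheduled four-weekly smears with smears taken because the subject was ill, so it can reflect clinic attendance as well as parasite control

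*Protocol*

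**What the plan says.** The analysis rule is in the Protocol, Section E, item 5: "Average parasitemia in all samples collected during the whole period will be compared between the vaccine and placebo group". Nothing in that item or elsewhere limits the average to one type of visit.

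Section D defines where the smears come from.

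- **Scheduled:** visits follow "Medical interview, consultation and serum sampling once every four weeks for 11 months", and each includes "A few drops of blood sampling (by finger prick) for malaria smear, filter paper blots, and ELISA assay".
- **Illness-triggered:** passive follow-up consists of "visits to LMC trial site whenever the subject is sick", and at those visits "a malaria smear will be done whenever malaria is suspected".

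The monthly questionnaire (Section N) allows for an illness to have been treated "In another hospital", so not every illness yields a smear at the site.

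On endpoints, Section A4.1 lists as primary "Change in titers of anti-SE36 antibody, parasitemia rates, malaria incidence, malaria treatment incidence density". The synopsis, under Outcome, names "prevalence of malaria parasitemia and parasite density for each group". Item 5 uses neither term; it gives only an average.

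**The concern.** The number of scheduled smears is set by the calendar and is the same for everyone who stays in the study. The number of sick-visit smears depends on how often a subject is ill, whether the subject comes to this site, and whether malaria is suspected. An average over both kinds gives most weight in summed density to the smears whose number is least controlled.

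Three consequences follow.

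1. Two groups with the same parasite biology can have different averages if they differ in how often illness leads to a site visit. The design does not assure equal attendance. Of the 66 controls, 48 are separately recruited volunteers who received nothing, while the vaccinees had already attended the site throughout Stage 2. Matching in Section D is by locality and addresses exposure, not care-seeking.
2. Even with equal attendance, a clinical episode enters the incidence endpoint and then enters again as a high density in this average. A difference cannot be attributed to parasite control between episodes rather than to the number of episodes.
3. The result is neither the prevalence nor the density by group that the synopsis promises.

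**Working it through.** **No design figure to reproduce.** The protocol gives no parasite prevalence, density, attendance rate, effect size or power for this comparison. Group sizes are consistent: 33 + 33 = 66 vaccinees; 9 + 9 + 48 = 66 controls; total 132.

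**Input from the protocol.** Four-weekly visits for 11 months: 11/12 × 365.25 / 7 = 47.8 weeks, and 47.8 / 4 ≈ 12 scheduled smears, so S = 12.

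**Assumptions (none is in the protocol).** Scheduled prevalence p = 0.3; density of a positive scheduled smear Ds = 500/µl; malaria illnesses per subject m = 1; density when ill with malaria Dm = 10,000/µl; other suspected illnesses o = 1, carrying background parasitaemia p × Ds = 150; a = share of illnesses brought to the site.

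**Formula.** Pooled mean = [S·p·Ds + a(m·Dm + o·p·Ds)] / [S + a(m + o)] = [1,800 + 10,150a] / [12 + 2a].

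**Same biology, attendance varied:**

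| a | Numerator | Denominator | Pooled mean |
|---|---|---|---|
| 0.50 | 6,875 | 13.0 | 529 |
| 0.65 | 8,397.5 | 13.3 | 631 |
| 0.70 | 8,905 | 13.4 | 665 |
| 0.75 | 9,412.5 | 13.5 | 697 |
| 0.90 | 10,935 | 13.8 | 792 |

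- Equal attendance: ratio 1.00.
- 75% versus 65%: 697 / 631 = 1.10.
- 90% versus 50%: 792 / 529 = 1.50. With p at 0.2 or 0.4, m from 0.5 to 2 and o from 0 to 2, this ratio runs from 1.32 to 1.61.
- At a = 0.70, sick-visit smears are 1.4 of 13.4 (about 10%) but 7,105 of 8,905 (about 80%) of summed density.
- Scheduled smears only: 150 in both groups, ratio 1.00, in this model.

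**Attendance against a true effect.** Cut both densities by 30% in vaccinees. Equal attendance gives 0.70. Vaccinees at 90% and controls at 50% give 0.7 × 792.4 / 528.8 = 1.05. The reverse gives 0.7 × 528.8 / 792.4 = 0.47.

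**Double counting with equal attendance.** Cut only the number of episodes by 30% (m = 0.7, a = 0.7): (1,800 + 0.7 × 7,150) / (12 + 0.7 × 1.7) = 6,805 / 13.19 = 516, and 516 / 665 = 0.78. The average falls by 22% although routine parasitaemia has not changed.

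**Dilution.** Take 12 scheduled smears averaging 1,000/µl (assumed). Adding 3 smear-negative sick visits gives 12,000 / 15 = 800; adding 6 gives 12,000 / 18 = 667. Extra attendance can therefore lower the average too.

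**Does a log scale cure it?** A simulation of 66 versus 66 subjects with no true effect compared subject means of log10(density + 1) by t-test, 400 replicates per setting, with prevalence and episode rates varying between subjects. The pooled mean was significant at the 5% level in 4% to 5.5% of replicates with equal attendance (70% in both groups). At 90% versus 50% attendance, this was 12%, 30% and 42% for an average of 1, 2 and 3 malaria illnesses per subject. The scheduled-only mean stayed between 3% and 7.5% in all nine settings. A log scale does not remove the problem.

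**The case against.** **The size is assumed.** This stands. A reader might infer that the comparison does measure attendance as much as parasite control. The protocol does not support that: it has no attendance or density figures, a modest gap gives about 1.10, and equal attendance gives no spurious difference. Section D also provides locality matching, home temperature recording and interviews about malaria between visits. These do not equalise attendance, but they show that the study is not indifferent to it.

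**More malaria visits mean more malaria.** This stands in part. A reader might illustrate the fault by adding malaria episodes to one subject's average: 12 smears at 1,000/µl plus one at 20,000/µl gives 32,000 / 13 = 2,462. That changes disease burden, not attendance alone, so it is not evidence of bias. The attendance model and the smear-negative case hold biology fixed, and they carry the point.

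**Scale and clustering.** A reader might infer an arithmetic mean, or that repeated smears from one child count as independent. Item 5 says neither, and both may properly be left to an analysis plan.

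**Which controls?** Item 5 names the placebo group for the average and the control groups only in its parenthesis on mild and severe episodes. Read literally, the comparator is the 18 saline recipients, and the argument from the 48 untreated volunteers falls away. Section B2.3 calls the two groups equivalent, so the wider reading is also possible.

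**Not labelled primary.** This stands. Item 5 sits under the aim on duration of antibody response. Its link to the parasitaemia rates in A4.1 is by inference, although no clearer analysis of them is given.

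**A detail for the analysis plan.** This fails. The protocol fixes which samples enter the average, and an analysis plan that separated them would depart from its text.

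**Conclusion.** The concern holds in limited form. As written, item 5 pools calendar-driven and illness-driven smears. The resulting average mixes routine parasitaemia, episode frequency and site attendance, and does not estimate the synopsis outcome.

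The double counting of episodes and the mismatch with the synopsis do not depend on any attendance gap. Spurious between-group differences do: about 1.10 at 75% versus 65% and about 1.50 at 90% versus 50%, on assumed prevalence, densities and illness rates. A gap of the larger kind could hide or exaggerate a true 30% effect, but nothing in the protocol shows that one will occur. The direction cannot be predicted either.

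This is a should-fix. The study is observational, incidence and treatment density are separate endpoints, and the tie to the primary endpoint is inferred.

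**What to change.** Reword item 5 so that:

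1. the between-group comparison of parasite prevalence and log density uses only the scheduled four-weekly smears and allows for repeated measures within subject;
2. sick-visit smears serve the incidence and severity endpoints, with density at clinical episodes reported separately;
3. any average over all samples is labelled descriptive;
4. the comparator is stated: the 18 placebo recipients or the full control group of 66.

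The cost is wording, provided the record for each smear shows the type of visit. No extra visits or samples are needed.

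There are two drawbacks. The density analysis has fewer smears. Scheduled smears are also not wholly free of attendance, because treatment at a sick visit can clear a later smear. If each treated episode cleared one of the 12 (an assumption), 90% versus 50% attendance would give (12 − 0.9) / (12 − 0.5) = 0.97 with one episode per subject and (12 − 2.7) / (12 − 1.5) = 0.89 with three. The one-episode figure compares with 1.50 for the pooled average, so the residual effect is much smaller, but it should be acknowledged when results are interpreted.

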## **F. Use, Storage, and Tracking of Specimens (blood samples) and Data**

Samples and data collected under this study will be used to study malaria, long term protection/immunity as induced by BK-SE36, and (whenever possible) molecular genotyping of *P. falciparum* in the study area. Access to the blood samples and data will be limited either using a locked room, a locked freezer, or a locked cabinet. Only investigators or their designees will have access. Any loss or unanticipated destruction of specimens (for example, due to freezer malfunction) or data (for example, lost of printed data or original source document with identifiers) will be reported to MBL-IRC and RIMD, Japan. Serum samples will be kept both in LMC, Lira and in RIMD, Japan; the transportation and storage of which will be tracked. Storage of all study-related documents will be such that confidentiality will be strictly maintained.

## **G. Protection of Human Subjects**

### **G.1. Institutional Review Board/Ethics Committee**

IRB approval will be obtained for the study. Documents will be submitted to the IRB as well as to the UNCST.

### **G.2. Informed consent**

In obtaining and documenting informed consent, the Investigator complies with applicable regulatory requirements, Good Clinical Practices and ethical principles. The written informed consent form is to be approved by the IRB prior to use.

### **G.3. Precautions**

None.

### **G.4. Benefits**

There will be no direct benefit from participation in this study. It is hoped that the information gained will contribute to the development of a safe and effective malaria vaccine.

## **G.5. Payment**

Subjects will be paid via LMC based on Ugandan standards. Compensation will cover for time spent, meal (s) and travel costs at each visit. Details will be available in the Informed Consent Documents.

## **H. Confidentiality**

Subjects will be assigned a unique subject code. All results will be linked to this number. Trial records will only be available to staff members and all related study information will be stored securely at the trial site. Access to files may be reviewed by representatives from RIMD, MBL-IRC, UNCST for monitoring purposes.

## **I. Publication**

It is anticipated that results of this study will be presented to the scientific community via oral presentations at meetings and written publications in scientific journals. The data to be presented and the authorship will be discussed between investigators and approved prior to any official communication.

## N. Questionnaire for Stage2 follow-up period; (Doctor's consultation guide)

|                                                                                                                         |  |               |  |
|-------------------------------------------------------------------------------------------------------------------------|--|---------------|--|
| Subject code                                                                                                            |  | Date of Visit |  |
| Residence:  Same as last time
 Moved to new house_(new address)_____ |  |               |  |

|                                                                                                                                                                                                                                                                                                                                                                                                                                                                                                                                                                                                                                                                                                                 |
|-----------------------------------------------------------------------------------------------------------------------------------------------------------------------------------------------------------------------------------------------------------------------------------------------------------------------------------------------------------------------------------------------------------------------------------------------------------------------------------------------------------------------------------------------------------------------------------------------------------------------------------------------------------------------------------------------------------------|
| Medical History                                                                                                                                                                                                                                                                                                                                                                                                                                                                                                                                                                                                                                                                                          |
| 1. Malaria history from last visit:  None  Yes (date)_____
1.1 Are there other household members who are suffering from malaria?
 None  Yes,( number)_____
1.2 Use of mosquito bednet while sleeping:  No  Yes
1.3 Was the mosquito net used soaked or treated with an insecticide to kill or repel mosquitoes?
 No  Yes
1.4 Has anyone sprayed the interior of the house against mosquitoes?  No  Yes                                        |
| 2. No of days symptomatic before diagnosis was made:  Not known  _____ days                                                                                                                                                                                                                                                                                                                                                                                                                                                                                                                                                                                     |
| 3. Treatment obtained:  In another hospital  In the trial site previous visit
Details (include self medications)                                                                                                                                                                                                                                                                                                                                                                                                                                                                                                                                             |
| Presenting features:
 Fever  Malaise  Headache  Joint pains
 Vomiting  Cough  Diarrhoea  Respiratory Distress
 Pallor  Jaundice  Bleeding  Abdominal Pain
 Sweating  Bleeding  Convulsions  Drowsy/Lethargy
 Rigor  Other (please specify) _____ |
| Blood smear:  Negative  Positive _____                                                                                                                                                                                                                                                                                                                                                                                                                                                                                                                                                                                                                          |
| Relevant Laboratory Results:                                                                                                                                                                                                                                                                                                                                                                                                                                                                                                                                                                                                                                                                                    |
| Present Visit/Diagnosis  Fine  Not Fine                                                                                                                                                                                                                                                                                                                                                                                                                                                                                                                                                                                                                         |
| 1. No of days symptomatic before this visit:  Not known  _____ days                                                                                                                                                                                                                                                                                                                                                                                                                                                                                                                                                                                             |
| Presenting features:
 Fever  Malaise  Headache  Joint pains
 Vomiting  Cough  Diarrhoea  Respiratory Distress
 Pallor  Jaundice  Bleeding  Abdominal Pain
 Sweating  Bleeding  Convulsions  Drowsy/Lethargy
 Rigor  Other (please specify) _____ |

Blood smear: ☐ Negative ☐ Positive \_\_\_\_\_

Vital Signs:

|                                                |                  |                |  |
|------------------------------------------------|------------------|----------------|--|
| Body weight (kg)                               | Body height (cm) |                |  |
| Blood pressure /  mmHg | Pulse rate bpm   | Body Temp (°C) |  |

Relevant Laboratory Results: ☐ Not Applicable

Management /Treatment/Prescriptions (including dosage and frequency):

Outcome:

At the end of this consultation, we request that a few drops of blood from a finger/earlobe be drawn. The test uses disposable sterile instruments that are clean and completely safe. The blood will be used for immunogenicity tests and the results of the test will not in anyway breach your (or your child's) confidentiality.

